# Motor Imagery to Facilitate Sensorimotor Re-Learning (MOTIFS) after traumatic knee injury: study protocol for an adaptive randomized controlled trial

**DOI:** 10.1186/s13063-021-05713-8

**Published:** 2021-10-21

**Keywords:** Knee injury, Rehabilitation, Exercise therapy, Return to recreational activities, Psychology, Sports psychology

## Abstract

**Background:**

Treatment following traumatic knee injury includes neuromuscular training, with or without surgical reconstruction. The aim of rehabilitation is to restore muscle function and address psychological factors to allow a return to activity. Attention is often on rehabilitation of knee function, but deficiencies often persist. Specific interventions addressing psychological factors are sparing with varying degrees of success. We have developed a novel training program, MOTor Imagery to Facilitate Sensorimotor Re-Learning (MOTIFS), which integrates simultaneous psychological training into physical rehabilitation exercises. The MOTIFS model individualizes rehabilitation to increase central nervous system involvement by creating realistic and relevant mental images based on past experiences. We hypothesize that a 12-week MOTIFS training intervention will improve psychological readiness to return to activity and muscle function to a greater extent than current neuromuscular training (Care-as-Usual).

**Methods:**

This pragmatic 1:1 single assessor-blinded adaptive cumulative cluster-randomized controlled trial will include 106 knee-injured people with a goal of returning to physical activity. Participants are randomized to either the MOTIFS or Care-as-Usual condition. Primary outcomes are the ACL Return to Sport after Injury Scale and change in injured leg hop performance in a side hop task from baseline to 12 weeks. Secondary outcomes include patient-reported outcomes and assessment of muscle function using a hop test battery and Postural Orientation Errors at 12-week follow-up. At 12-month follow-up, patient-reported outcomes are assessed. A sub-group (7-10 in each group) will be interviewed to gain insight into experiences of rehabilitation.

**Discussion:**

Strengths of this trial include that it is a randomized and pragmatic trial examining commonly under-studied aspects of rehabilitation following a knee injury. The model uses the patient as a reference, creating simultaneous psychological and physical training exercises with easily adopted principles for clinical practice. Limitations include that blinding is limited due to study design, and shifting the clinical paradigm to a more holistic model is a challenge. If successful, the MOTIFS model has implications for a clinically useful, individualized, and patient-relevant method of improving rehabilitation outcomes by integrating psychological training into physical training.

**Trial registration:**

ClinicalTrials.gov NCT03473821. Registered March 22, 2018, with ethical approval that has been granted (Dnr 2016/413, Dnr 2018/927).

**Trial status:**

Trial Status: Protocol Version is 2020, Dec 10 – Version 1

**Supplementary Information:**

The online version contains supplementary material available at 10.1186/s13063-021-05713-8.

## Background

Treatment following a traumatic knee injury, such as to the anterior cruciate ligament (ACL), [1] meniscus [2], or patella [3], includes training with or without surgical intervention, with the goal of returning to pre-injury or modified activity levels. Despite current best-evidence treatment, many knee-injured people have poor patient-reported outcomes, such as perceived poor knee function and fear of re-injury, which are associated with poor rehabilitation outcomes in terms of lower return to physical activity [4]. Persistent sensorimotor deficiency has also been shown in the form of reduced muscle strength and hop performance [5] and undesirable postural orientation [6] in people with an ACL injury. In people with meniscal tears, reduced knee function and strength have been observed [7]. Poor muscle function in terms of limb asymmetry between the injured and uninjured legs in hop performance is associated with a lower probability of returning to pre-injury activity levels [8]. Reaching normal muscle function is, therefore, commonly considered an important milestone in returning to desired physical activity levels [9]. A meta-analysis and systematic review showed that people that returned to normal or nearly normal knee function (≤10% side-to-side difference) following ACL injury were more likely to return to activity, though only 65% of the total ACL-injured population returned to their preinjury level of sport, and 55% returned to competitive level sport [8]. Based on these results, factors other than muscle function are likely important for return to activity, and/or rehabilitation does not sufficiently prepare people for return to sport or physical activity.

Recent best-evidence recommendations have suggested that rehabilitation programs should focus on rehabilitation of the physical function of the knee and address psychological factors in order to improve the quality of life and prevent subsequent knee injuries/problems [9]. However, the majority of attention is on rehabilitation of physical function of the knee, using neuromuscular and strength training to reduce joint effusion, increase range of motion, and improve muscle strength, hop performance, and control of movements in weight-bearing positions [9]. Importantly, both physical and psychological factors are linked to rehabilitation outcomes. A systematic review and meta-analysis have shown that better muscle function such as hop performance, as well as positive psychological responses was associated with a higher likelihood of return to sports [8]. Research has also shown that higher self-efficacy, reduced fear of re-injury, and greater satisfaction with knee function are associated with better knee function and higher likelihood of return to physical activity [10]. Increasing focus on psychological interventions is important, as a knee injury is not purely physical, but requires a more holistic approach.

In uninjured people, psychological interventions both improve psychological outcomes [11] and increase central nervous system activation [12]. This increased activation could potentially address plastic changes in the brain, a suggested underlying cause of persisting sensorimotor deficiencies in people with an ACL injury [13]. Thus, a knee injury represents not only a musculoskeletal injury, but a neurophysiological dysfunction which may result from damage to the somatosensory system [14]. Specific psychological interventions to improve rehabilitation outcomes following knee injury are, however, sparing and with varying degrees of success, often performed completely separate from physical interventions. A systematic review of only four studies on psychosocial interventions in addition to separate knee rehabilitation, using static guided imagery and relaxation, or watching coping or therapeutic videos, noted improved self-efficacy, but with conflicting results for fear of re-injury/re-injury anxiety [15]. The mechanisms for these associations are unknown, which warrants more thorough investigation into other psychosocial interventions to optimize treatment outcomes. A potential solution may be more holistic rehabilitation programs in which consideration is given to the localized physical trauma, as well as to the central nervous system changes and the overall psychological aspects of the injury.

Currently, it is not known which psychological intervention has the greatest potential to improve outcomes in injured people. In uninjured people, sports psychologists use a set of training tools known as psychological skills training to enhance performance. The most common techniques used include goal-setting, arousal regulation, self-talk, and imagery [16]. Imagery is the practice of using one’s own memories and experiences to create a mental picture of a situation, without actually executing the movement [17]. Imaging while focusing on contextual, tactical, and kinesthetic aspects is referred to as “motor imagery” [17]. This can be done while sitting or standing still with little to no physical movement, known as static imagery. Dynamic motor imagery (DMI) is the practice of imaging a specific situation while simultaneously physically mimicking part or all of the movement in order to increase realism [17]. The aim is to improve performance by creating a functionally equivalent image of a relevant and activity-specific movement [18]. Functional equivalence in this sense means that the movement being performed is as close as possible to actual execution by focusing on Physical, Environmental, Task, Timing, Learning, Emotion, and Perspective (known by the acronym PETTLEP) [18].

In uninjured athletes, physical training with no imagery, only static imagery, and only DMI have all resulted in performance enhancement, although performance benefits appear to be optimized when DMI is combined with physical training [19]. According to Self-Determination Theory, motivation can be increased using an autonomous contextual decision-making process, individual connection to the activity, and by applying one’s own competencies [20], all of which can be accomplished using DMI.

Shifting the focus to individual relevance may influence motor learning and performance of experienced-based movements, according to the OPTIMAL theory of motor learning [21]. This is also supported by the theory of re-investment, which states that motor execution can be disrupted through attempts at conscious control [22]. For example, focusing on how to execute a situation-based (i.e., soccer) task, rather than on movement technique, relies more on automatic processes to create efficient movement [22]. A more external focus also creates an understanding of the applicability of the movement, shifting motivation from extrinsic (outcome-oriented) to intrinsic (inherent satisfaction), which is important for adherence [23]. Adherence may then also influence physical outcomes by virtue of having performed the exercises [24].

Integrating DMI into knee-injury rehabilitation constitutes a potential alternative to improve the effectiveness of rehabilitation by targeting a gap in the rehabilitation literature. This allows for specific interventions that can be used in a clinical environment which aim to address and affect physical, neurological, and psychological aspects.

This study protocol describes an ongoing adaptive randomized controlled trial, the aim of which is to compare the efficacy of rehabilitation with integrated dynamic motor imagery, and rehabilitation alone (care-as-usual) in terms of improving both muscle function and patient-reported outcomes in physically active males and females with a traumatic knee injury and with a goal of returning to physical activity. This approach of integrating physical and psychological aspects in rehabilitation takes a holistic perspective of the injury, in contrast to an isolated physical perspective in care-as-usual rehabilitation.

The main hypothesis is that 12 weeks of rehabilitation with integrated dynamic motor imagery will improve patient-reported psychological readiness to return to physical activity and objective muscle function to a greater extent than CaU rehabilitation.

Secondary aims include examining the effect of rehabilitation with integrated DMI on patient-reported outcomes, performance in a hop battery, and postural orientation. The exploratory aims include a phenomenological interview with patients to gain further insight into the perceived experiences throughout the rehabilitation process.

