#### Main outcomes

This trial includes two main outcomes. Psychological readiness to return to sport is evaluated using the Swedish version of the ACL-Return to Sport after Injury scale (ACL-RSI), which includes an emotional response, confidence, and risk-appraisal when returning to sport after an ACL injury [33, 34]. Physical function is evaluated using the change in number of hops in the injured leg from baseline to 12 weeks for the side hop task.

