### Statistical analyses

#### Sample size

Based on previous studies examining ACL-RSI [49] and side-hop function [50], a preliminary sample size was estimated, to be used in the first phase of this adaptive RCT, which resulted in *n*=106 participants. This included adjustments for potential cluster effects using a preliminary Intra-Cluster Correlation Coefficient (ICC). An approximation is required as comparable studies are unavailable to reliably perform a sample size estimation. This is necessary in this phase in order to evaluate whether an intervention effect is detectable and within practical limitations, which will thereafter inform more accurate sample-size estimations.

A new sample size will be calculated by a blinded third-party member of the data management committee using collected data from an interim analysis, therefore allowing for more accurate between-group differences in the main outcomes. Observed within- and between-cluster variance will also be calculated in order to more accurately estimate an Intra-Cluster Correlation Coefficient (ICC, denoted as *ρ*). This will be performed using the formula $$ \rho =\frac{s_b^2}{s_b^2+{s}_w^2} $$ [51] in order to adjust for the fact that different clinics are included in the trial (i.e., potential clustering effects). The adjusted sample size will therefore be calculated using the formula $$ \frac{n_ik\left(1-\rho \right)}{k-{n}_i\rho } $$ [52], along with an estimated 20% drop-out rate, in order to reach a power of 0.80, with significance set at *p*<0.025. As an estimated sample size has been calculated, the new sample size will only be adjusted up; that is, the number of participants included will not be less than *n*=106 required in the original sample-size estimation.

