#### Data analysis

The analysis will be done using the IBM SPSS statistical software package (IBM Corp., Armonk, New York, USA). Primary analyses of the entire sample will be done according to intention-to-treat principles. A dose-response analysis will be performed to determine effective adherence. Per-protocol analyses will be performed for those participants with at least 70% adherence (corresponding to two trainings per week), as a preliminary estimate of the effective number of training occasions. This is in order to eliminate cross-over and drop-out effects in the total sample, as well as to evaluate the training for those that have reached a pre-defined level of adherence deemed acceptable to have an effect. Sensitivity analyses will be performed to determine whether within-cluster correlations indicate potential effects due to being clustered, for example, by the clinic or by PT. Patient cross-over (i.e., patients changing clinics) is a low-risk possibility and will be recorded in case of occurrence. All outcome variables will be examined for normality using appropriate testing (e.g., Kolmogorov-Smirnov). Complete-case analyses are the primary analyses, and sensitivity analyses will be done depending on the number of missing values. Missing values are not expected to be extensive, and if less than 5% of data is missing, the whole data set will be analyzed along with a sensitivity analysis with appropriate imputed values. If between 5 and 40% of data is missing, appropriate multiple imputation methods will be used, which will be informed by blindly assessing results of the interim analysis, and a complete-case analysis will be done with appropriate sensitivity analyses. If over 40% is missing, a complete case analysis will be done with no sensitivity analysis.

Results will be analyzed using independent samples *t* tests to examine between-group differences of the change from baseline to a 12-week follow-up. Where appropriate, equivalent non-parametric Wilcoxon signed-rank testing will be used to compare between-group differences. The main analysis will focus on the two main outcomes, with secondary outcomes acting as support for these. Secondary outcomes therefore carry less weight and issues with potential error due to the number of evaluations will be discussed when results are presented.

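### The main hypothesis claims superiority on both main outcomes, the 0.025 level looks like an either-or split, and a result significant on only one outcome has no stated conclusion

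*Protocol article*

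**What the plan says.** - Background: the main hypothesis is a single sentence, that the intervention "will improve patient-reported psychological readiness to return to physical activity and objective muscle function to a greater extent than CaU rehabilitation". The Abstract joins the two outcomes in the same way.
- Main outcomes: "This trial includes two main outcomes", namely ACL-RSI and the change in side hops on the injured leg. They are not ranked or weighted.
- Sample size: the re-calculation is done "in order to reach a power of 0.80, with significance set at" p<0.025. No reason or sidedness is given for that level, and the power is not labelled as per outcome or joint. The starting figure of 106 is preliminary and can only be raised.
- Adaptive design modification criteria: the trial continues unmodified if the ACL-RSI criterion and/or the side-hop criterion is met, each judged separately. This is an interim rule. A Bonferroni correction is named there, but for repeating the pilot phase and not for having two outcomes.
- Data analysis: "The main analysis will focus on the two main outcomes, with secondary outcomes acting as support for these". The section gives no significance threshold and no rule for combining the two results.

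**The concern.** A claim that the intervention is better on A and on B is supported only when both tests are significant. Each test can then use the full 0.05, because requiring both already controls the error. A claim that it is better on A or on B needs the 0.05 to be divided. The article words the first kind of claim and uses a level that fits the second.

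The case that matters is exactly one significant outcome. The same data could then be reported as success on a main outcome or as failure of the main hypothesis, and the choice would be made after the results are known. A split is plausible here. ACL-RSI is self-reported by participants who cannot be blinded, whereas the side hop is counted by a blinded test leader.

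The planned re-calculation is also affected, since the sample size that gives 0.80 depends on which claim is being powered.

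**Working it through.** **The plan's own figure.** The 106 cannot be reproduced, because the effect sizes, standard deviations, intra-cluster correlation and number of clusters are not given. Solved backwards without clustering, at two-sided 0.025 and 80% power, with d = 2 × (2.241 + 0.842)/√N:
- N = 106 analysed: 6.166/10.296 = 0.60.
- N = 106 × 0.8 = 84.8 after the 20% drop-out: 6.166/9.209 = 0.67.

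This shows only what 106 could mean.

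**What 0.025 fits.** Two tests at 0.025 sum to 2 × 0.025 = 0.05, the usual division for an either-or claim.

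**Inputs for the power check.** From the article: level 0.025, power 0.80, two main outcomes. Assumed: 0.025 is two-sided and equals 0.05/2, 0.80 is power per outcome, both outcomes have equal power, and the two test statistics are bivariate normal with correlation r. The article does not give r, so a range is used.

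**Formulas.** Each statistic has mean 2.241 + 0.842 = 3.083, so it exceeds 2.241 with probability 0.80.
- Both at 0.025: B = P(Z1 > 2.241 and Z2 > 2.241). At r = 0 this is 0.80² = 0.64.
- At least one: 0.80 + 0.80 − B. At r = 0 this is 0.96.
- Exactly one: 1.60 − 2B. At r = 0 this is 0.32.
- Both under Holm at 0.05: P(both exceed 1.960) minus P(both lie between 1.960 and 2.241). At r = 0 this is 0.869² − 0.069² ≈ 0.751.
- Power per outcome under Holm: half of (at least one + both under Holm). At r = 0 this is (0.960 + 0.751)/2 ≈ 0.855.

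| r | Both, 0.025 each | Exactly one, 0.025 each | At least one | Both, Holm | Per outcome, Holm |
|---|---|---|---|---|---|
| 0 | 64.0% | 32.0% | 96.0% | 75.1% | 85.5% |
| 0.3 | 66.6% | 26.8% | 93.4% | 76.6% | 85.0% |
| 0.5 | 68.7% | 22.6% | 91.3% | 77.8% | 84.6% |
| 0.8 | 72.9% | 14.2% | 87.1% | 80.4% | 83.7% |

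The chance of at least one significant outcome is the same under Holm, because its first step is still the smaller p against 0.025.

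**Unequal power.** If one outcome has 80% power and the other 90%, the chance that both are significant at 0.025 is 72–75% for r from 0 to 0.5. With 95% for the other it is 76–78%. With one outcome at 80%, it cannot exceed 80%.

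**Effect on sample size.** Scaled from 106 under the equal-power assumptions, 80% power for both outcomes needs about 130–136 participants at 0.025 each, or 110–115 at 0.05 each (r from 0.5 to 0).

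**The case against.** The strongest reply is that the conjunction is ordinary prose listing two expected benefits, not a formal both-must-win test. The interim rule treats the outcomes separately, which supports an outcome-by-outcome reading with a natural conclusion for a split result. Testing each at two-sided 0.025 would then be valid, and Holm only more efficient. Under a both-required reading it would be conservative, not wrong. Success rules are also commonly left to an analysis plan, which is not shown.

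Much of this stands. The missing success rule would not be a finding on its own, and a fixed split is not an error. But the interim rule governs continuation and not the final claim, and the printed hypothesis still says something different from the outcome-by-outcome reading. If that reading is intended, the hypothesis should say so.

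A reader might infer that the article has adopted an either-or split and so contradicts itself outright. It does not support that. The 0.025 appears only as an input to the sample-size re-calculation, without a reason. It could be an unsplit one-sided level or be related to the correction for a repeated pilot, although that correction is described as applied after the initial interim analysis.

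**Conclusion.** The point holds as a mismatch between the hypothesis wording and a level consistent with an either-or split, with no stated conclusion for a split result. If each outcome has 80% power at two-sided 0.025, a split has a probability of 14–32% for correlations from 0.8 down to 0, and the hypothesis as worded has 64–73% power.

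A reader might go further and infer that the stated 80% power is false. The article does not support that. It never says whether 0.80 is per outcome or joint, it attaches the figure to a future re-calculation, and the inputs for 106 are absent. The direction is firm if 0.80 is per outcome: joint power is below 80% unless the two tests are perfectly correlated or the other outcome is certain to be significant. The size depends on assumptions.

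**What to change.** 1. In the Abstract and Background, state one hypothesis per main outcome. Limit claims to the outcome or outcomes rejected, and allow a claim of improving both readiness and muscle function only if both are rejected.
2. In the Sample size section, give the reason for 0.025 and its sidedness.
3. If 0.025 is the split over two outcomes, replace the fixed level with Holm at a two-sided family-wise 0.05: test the smaller p against 0.025 and, if it is significant, the other against 0.05. If the Bonferroni correction for a repeated pilot applies, run Holm at the reduced family-wise level. Holm rejects whatever the fixed split rejects and sometimes more, with the same family-wise error control.
4. Label the 0.80 as per outcome or joint, and base the re-calculation on the same rule. Give any joint power only as a range with its assumptions.

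The cost is a few sentences, with no extra participants or data for the wording and Holm changes. If the 0.80 is declared joint, the re-calculated sample size may rise. The rule should be fixed before comparative data are seen. The article reports 35 participants included, and the interim analysis waits for 25 in both groups (50 in all, if that means 25 in each).
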